## Approach

The traditional research pipeline that is a phased approach to moving interventions from efficacy trials to the real world can take a long time and inhibit the application of research knowledge in a real-world setting. To speed this process, BSMART proposes to use a Type 2 hybrid effectiveness-implementation study design to simultaneously test effectiveness and implementation strategies of existing and evidence-based smoking cessation interventions. Targeted adaptation of these interventions will be informed by our in-depth understanding of the local context and deep-rooted reach into existing HIV care infrastructure for effectiveness and supplemental qualitative data to identify barriers/facilitators in order to assess adoption and implementation factors. The durability/maintenance of the implementation will be examined, and cost-effectiveness to inform the MOHW and the Botswana National AIDS and health promotion agency (NAHPA) will be assessed.

## Innovation

The tobacco epidemic is one of the largest public health threats the world has ever faced, killing more than 8 million people a year globally. Yet, interventions in LMIC have been left frustratingly behind. We also argue that the well-funded HIV care system presents a unique opportunity to integrate smoking cessation interventions and move tobacco control into the global conversation. The primary innovation of this study is focused on improving not only smoking cessation among PLWH but also the facilities' capacity and coalitions to maintain the integrated intervention. Post-intervention follow-up will help us understand durability of the implementation. This project is a rare example of a care team intervention focusing on LHWs and task-shifting in the LMIC context. The trial itself will precisely quantify key indices of implementation strategies while also providing effectiveness of interventions.

## Methods

### Study Design

We will utilize a stepped wedge cluster randomized trial to implement BSMART. BSMART will be sequentially rolled out to 15 participating HIV treatment and care facilities assigned in three steps (Table 1). Each step will provide data for a 12-month control/pre-implementation, a 12-month implementation, and a 12-month maintenance period. We will stratify Botswana's HIV treatment and care facilities into three levels of facilities. We will randomly assign each of the three levels of facilities to one of three study steps. Each step will comprise (i.e. have representation) from three levels of facilities, giving each level of facilities the same probability of beginning the intervention at any step). We choose this design to:

- 1) minimize the practical, logistical, and financial constraints associated with large-scale project implementation,
- 2) control for the effect of time, and
- 3) ensure that all HIV treatment and care practices will eventually offer the intervention and assess maintenance.

The study will screen approximately 6,900 HIV-infected patients and we expect to enroll 750 eligible participants, 375 of whom will participate in the pre-implementation phase and 375 of whom will participate in the implementation phase across three waves of implementation at five facilities each.

| Table 1: Time Periods for Stepped Wedge Implementation |                                                  |         |                |                |                |             |
|--------------------------------------------------------|--------------------------------------------------|---------|----------------|----------------|----------------|-------------|
| Steps                                                  | Total Number of Participants                     | Year 1  | Year 2         | Year 3         | Year 4         | Year 5      |
| 1                                                      | 5 facilities, n=250 PLWH (1DH, 2 PHs, 2 clinics) | Control | Implementation | Maintenance    |                |             |
| 2                                                      | 5 facilities, n=250 PLWH (1DH, 2 PHs, 2 clinics) |         | Control        | Implementation | Maintenance    |             |
| 3                                                      | 5 facilities, n=250 PLWH (1DH, 2 PHs, 2 clinics) |         |                | Control        | Implementation | Maintenance |

## Study Population

Participants will be drawn from the population of HIV-infected patients receiving care at 15 selected health facilities that are part of the Accelerating Botswana through the Last Mile to Epidemic Control (ABLE) project. We plan to screen approximately 6,900 HIV-infected patients (230 PLWH per facility per year) for tobacco smoking and subsequently identify 750 patients who are interested in quitting into the trial, a total of 375 of whom will participate in the control period and 375 of whom will participate in the implementation period across three waves of implementation at five facilities each. Study participants will receive HIV care and treatment according to national standards.

Eligibility criteria: To maximize “real world” practice we attempted to err on the side of inclusivity in the study’s eligibility criteria. We will apply the following inclusion criteria:

- (1) HIV-infected,
- (2) self-reported current daily smoker,
- (3) age 18 years and older,
- (4) engaged in HIV care as defined by being on ART for at least 6 months at one of 15 selected health facilities (or four reserve facilities), and
- (5) willing/able to provide informed consent in English or Setswana.

We will apply the following exclusion criterion:

- (1) pregnancy or nursing

We acknowledge that patients living with HIV/AIDS in real-world treatment settings use other substances in addition to tobacco and will often have some problems associated with that use. To limit this study to those who smoke tobacco only means tailoring the intervention to a small group that is not truly representative of the larger population of PLWH.

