## Study Treatment/ Intervention

### **Screening, Brief Intervention, and Referral to Treatment (SBIRT).**

SBIRT is a comprehensive, integrated, public health approach to the delivery of early intervention and treatment services for persons with substance use disorders. The utility of SBIRT for all forms of tobacco use, especially smoking, has been endorsed by the U.S. Preventive Services Taskforce. We will use a SBIRT approach to promote smoking cessation using the 5 “A”s (Ask, Advise, Assess, Assist and Arrange for Follow-up) that has been used in multiple settings and found to be particularly effective with tobacco and alcohol-use disorders.

**Screening and brief intervention:** Trained LHW case managers will oversee the screening and brief intervention procedures (i.e., the 5”A”s). The first “A” begins the intervention with the LHW “Asking” eligible clinic clients about smoking. When a participant reports being a daily smoker, the LHW will link the participant to a research assistant in the clinic who will obtain informed consent and enroll the smoker in the trial. The participant will return to the LHW case manager who will proceed to the next 3 “A”s (Advise, Assess, Assist). These 3”A”s will constitute the brief intervention. The LHW will utilize a motivational enhancing conversation focusing on increasing insight and awareness regarding smoking, offering information and Advice and Assessing motivation toward behavioral change. For those participants who are motivated for treatment, a referral (Assist) will be made to a clinic nurse prescriber (NPD) for evaluation for treatment with varenicline. For those not ready to make a quit attempt, the LHW will encourage consideration of quitting and Arrange for a follow-up conversation. A culturally acceptable standardized form will be integrated into intake procedures within the HIV clinic that will allow case managers to document implementation and outcomes of using the 5”A”s.

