## **Randomization methods**

We have chosen 15 (and 4 reserved) high-volume (>1000 HIV-positive patients currently active and on ART) health facilities (See Figure 4) in the ABLE project for inclusion based on numbers of patients, accessibility to the research team, and willingness to collaborate. After a baseline period of 1 year, the BSMART intervention will be implemented in a step of five new randomly selected sites (1 district hospital, 2 primary hospitals, 2 primary care clinics) until it is eventually implemented in all 3 steps (15 sites). A computer-generated list containing facilities stratified by type will determine the order in which the sites receive the intervention. The randomization list will be maintained by a statistician who is not involved in the study, and the site allocation will remain concealed from the research team and clinical teams throughout the study and will be revealed for a given step only 1 month before the implementation of the intervention to allow for training.

[figure not shown]

Figure 4: Selected and reserve facilities for BSMART project

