### Enrollment in BSMART study

At enrollment, research assistants will fill the demographic form, intake smoking history questionnaire and use the stages of change algorithm and readiness ruler to determine the individual's stage of change for quitting. Lay Health worker case managers will provide participants with the standard of care brochure which contains basic information on the risks of smoking and the need to stop smoking.

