## Statistical analysis

### Statistical Analysis for Study Objective 1.

We will analyze “Reach” as the percentage of PLWH who participated in the screening for tobacco use for each facility and compare between the control and implementation group using chi-square test. We will examine sociodemographic and clinical characteristics of smokers who did not participate. As analysis of primary outcome with intention-to-treat, the clinical effectiveness endpoint will be compared between the control group and implementation group at the individual level with a generalized linear mixed model with a binary distribution using the jack-knife method to estimate standard errors to account for grouping within clusters and by incorporating a log-link function to estimate the relative risk as a measure of effect. We will include random effects to account for the clustering within facilities and periods and fixed effects for type of facilities. The model will be selected as the best model with unique covariance structure that produces the lowest Bayesian Information Criterion (BIC) value. The covariance structures that will be considered in the model are the first order of autocorrelation covariance structure, unstructured covariance structure, and Toeplitz covariance structure. We will use the Satterthwaite method to adjust for denominator degree of freedom for the test for fixed effects. The random coefficients will be modeled using G-side random effects, and we will obtain the subject-specific estimates by defining the appropriate variance-covariance structures.

Sex-stratified and age-stratified analyses and models will be performed as secondary analyses. Given high quality of data and experience in conducting studies in Botswana, we do not expect to have missing observations in the variables required for the primary analysis. To address the concern about contamination, we will conduct a sensitivity analysis excluding patients in the control group in the 90 days before crossing over to the implementation group. Because there will be fewer than 50 clusters, we will conduct a sensitivity analysis using a small sample correction with the Kenward-Roger method.

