#### Characteristics of the study population:

Participants will be drawn from the population of HIV-infected patients receiving care at 15 selected health facilities that are part of the ABLE project (see Facilities and Other Resources). We plan to screen approximately 6,900 HIV-infected patients for tobacco smoking and subsequently enroll 750 patients who are interested in quitting tobacco smoking into the trial, 375 of whom will participate in the pre-implementation phase and 375 of whom will participate in the implementation phase across 3 waves of implementation at 5 facilities each. Study participants will receive HIV care and treatment according to national standards. Participants will be eligible to participate in the study if they meet the following criteria:

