#### Eligibility Checklist

| Inclusion Criteria |    |                                                                                          |
|--------------------|----|------------------------------------------------------------------------------------------|
| Yes                | No |                                                                                          |
|                    |    | Confirmed chart diagnosis of HIV and receiving treatment at the participating HIV clinic |
|                    |    | Current self-reported daily smoker                                                       |
|                    |    | Age 18 or older                                                                          |
|                    |    | Willing and able to provide informed consent in English or Setswana                      |
|                    |    |                                                                                          |
| Exclusion Criteria |    |                                                                                          |
| Yes                | No |                                                                                          |
|                    |    | Current pregnancy or nursing                                                             |
|                    |    |                                                                                          |

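### Each phase recruits its own participants with the phase known and under inconsistent entry wording, and the primary model names no participant baseline term to limit a difference in mix

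*Protocol*

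**What the plan says.** **Who is recruited, and by whom.** Study Design and Table 1 give every facility one control year and one implementation year, with 375 people enrolled in each phase overall. Participant sampling and recruitment has the LHW case manager apply the eligibility criteria; the research assistant then takes consent and enrols, first come, first served. Appendix A lists a separate consent form for each phase. Control participants get a brochure. Implementation participants get SBIRT counselling and, if motivated and cleared, varenicline from the study.

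**Entry rule.** Study Population says the study will "subsequently identify 750 patients who are interested in quitting into the trial", and the human-subjects section says it will "subsequently enroll 750 patients who are interested in quitting tobacco smoking into the trial". The smoking criterion in the list is only "self-reported current daily smoker". The SBIRT section sends any daily smoker to consent before motivation is assessed, and then provides: "For those not ready to make a quit attempt, the LHW will encourage consideration of quitting". The first item on the Appendix B1 checklist is "Confirmed chart diagnosis of HIV and receiving treatment at the participating HIV clinic"; no item asks about interest in quitting or about 6 months on ART.

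**Baseline data.** At enrolment in both phases, research assistants "use the stages of change algorithm and readiness ruler to determine the individual's stage of change for quitting". Appendix B3 collects the Fagerström items, including banded cigarettes per day, and Appendix B2 collects age and sex.

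**Primary model.** Statistical Analysis for Study Objective 1 specifies a mixed model with a log link, random effects for facility and period, and "fixed effects for type of facilities". Age and sex appear only in stratified secondary analyses. Stage of change is analysed only as a longitudinal outcome.

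**The concern.** The comparison is between different people, recruited after the phase is known, under offers of very different attraction. Cluster randomisation balances facilities over the order of roll-out; it does not balance which smokers in a facility accept a brochure and which accept counselling with free medication. If acceptors differ between phases in readiness to quit or in nicotine dependence, part of the observed difference in abstinence reflects who enrolled, not what BSMART did. The stated model has nothing at participant level to limit this, although the relevant variables are collected in both phases. The named sensitivity analyses deal with contamination and the small number of clusters, not with recruitment.

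The entry wording adds avoidable uncertainty, because staff who take the population paragraph literally would apply a filter that the criteria list and the checklist do not contain. Separately, B1 used as written would admit people on ART for less than 6 months, whom criterion 4 excludes.

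**Working it through.** **1. The plan's own figure.** Inputs from Power and Sample size: 10% versus 20% abstinence, 25 per cluster-period, 5% loss, ICC 0.02, two-sided test. The numeric alpha is not given; 0.05 is assumed. With 15 facilities:

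- n per phase = 375 × 0.95 = 356.25, or 23.75 per cluster-period
- design effect = 1 + (23.75 − 1) × 0.02 = 1.455
- effective n = 356.25 / 1.455 = 244.8 per phase
- power by the pooled two-proportion formula = 87.5%, against the stated 87%

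The stated figure reproduces, so 244.8 serves as the yardstick in step 3.

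**2. Shift from a difference in readiness, with no treatment effect.** The documents give neither quit rates by readiness nor the share of ready smokers. Assume 14% abstinence in ready and 6% in not-ready smokers, which averages 10% when half are ready. Then:

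shift = (ready share in implementation − ready share in control) × (0.14 − 0.06)

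| Difference in ready share | Shift in risk difference | Share of the 10-point target |
|---|---|---|
| 10 points | 0.10 × 0.08 = 0.8 points | 8% |
| 20 points | 0.20 × 0.08 = 1.6 points | 16% |
| 30 points | 0.30 × 0.08 = 2.4 points | 24% |

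The sign reverses if the ready share is lower in implementation.

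**3. Wider assumptions.** Hold control abstinence at 10%, let a share s of control enrolees be ready, and let ready smokers quit k times as often. The not-ready rate is 0.10 / (s·k + 1 − s), and the shift is the difference in share × (k − 1) × that rate.

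- Smallest case (s = 0.6, k = 2, difference 10 points): 0.10 / 1.6 = 0.0625; shift = 0.10 × 1 × 0.0625 = 0.6 points.
- Middle case (s = 0.5, k = 3, difference 20 points): 0.10 / 2.0 = 0.05; shift = 0.20 × 2 × 0.05 = 2.0 points, i.e. 10% versus 12%, relative risk 1.20.
- Largest case (s = 0.4, k = 4, difference 40 points): 0.10 / 2.2 = 0.0455; shift = 0.40 × 3 × 0.0455 = 5.5 points.

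If the middle case ran in BSMART's favour, the chance of a falsely significant benefit at effective n 244.8 would be 10.5% instead of 2.5%. If it ran the other way, it would hide 2 points of true benefit.

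**4. Is there room for a difference in mix?** The Protocol Summary puts smoking prevalence among people with HIV in the region at 12.5% to 44.3%. Of 6,900 screened, that is 863 to 3,057 smokers. Enrolling 750 takes between 750/863 = 87% and 750/3,057 = 25% of them, so acceptance can shape who is in the sample.

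**5. Can the data carry covariates?** With average abstinence of 15% (midway between 10% and 20%) in 750 × 0.95 = 712 participants, about 107 events are expected. That is enough for four to six baseline terms.

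**The case against.** **Covariate lists often sit in the SAP, which is not shown.** That is fair as far as it goes. But the protocol does state the terms of the primary model, and adjusting for variables already collected would improve on that model. The entry wording and B1 are protocol matters in any case.

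**A reader might infer that treating workers choose the participants.** The documents do not support this. A research assistant consents and enrols, first come, first served, and the listed criteria leave the LHW little discretion. What remains is mainly self-selection by participants who know the offer.

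**A reader might infer that the effect will be inflated.** Nothing in the documents shows a shift or its direction. Free medication could draw in the motivated; it could equally draw in the marginally motivated, while a brochure-only phase attracts the self-motivated.

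**A reader might infer that the entry wording itself creates bias between phases.** It applies equally to both, and a smoker can be interested yet not ready, a distinction the readiness ruler itself draws. The mismatch with the criteria list, the enrolment sequence and B1 still stands.

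**A reader might point to concealment.** Randomization methods says that "the site allocation will remain concealed from the research team and clinical teams throughout the study" until 1 month before implementation, while under Table 1 a facility opening its control year reveals its step. That tension does not drive this point: even with perfect concealment of the order, the phase is known when each participant is enrolled.

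**Readiness is recorded after phase-specific consent**, so it may already reflect the offer, and conditioning on it could remove some effect. This stands. Dependence, age and sex are cleaner adjusters, and readiness needs more care.

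**Conclusion.** The point holds as a vulnerability, not as demonstrated bias. Participant mix can differ by phase, randomising facilities does not prevent it, and the stated primary model has no participant baseline term to limit it. On the assumed 14% and 6% quit rates the consequence is 0.8 to 2.4 points either way; under wider assumptions it is 0.6 to 5.5 points. The planned effect is 10 points in Power and Sample size and 8 in the objectives. These sizes rest wholly on assumed readiness shares and quit rates. Adjustment would limit the problem only for factors that are measured, and measured well. Two documentary errors stand apart from the size: the population paragraphs do not match the criteria, the enrolment sequence or B1 on interest in quitting, and B1 lacks the 6-month ART criterion.

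**What to change.** 1. **Primary model.** Add Fagerström score (or cigarettes per day), age and sex as fixed effects. Use baseline stage of change or readiness ruler either in the primary model or in a prespecified adjusted analysis. State that readiness is recorded before any SBIRT contact beyond the Ask step, and acknowledge that it follows phase-specific consent. Report the model without covariates as a sensitivity analysis.
2. **Entry rule.** Reconcile the two population paragraphs with the listed criteria, the SBIRT section and Appendix B1, so that one rule on interest in quitting applies in both phases.
3. **Appendix B1.** Add the 6-months-on-ART criterion, to match the inclusion lists.

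The cost is analysis wording, a text reconciliation and one form edit. No new data and no change in sample size are needed. The technical price is that a log-link model with covariates may not converge; standardised risks from a logistic model can then supply the relative risk, and this should be written down in advance.

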## Study Treatment/ Intervention

### **Screening, Brief Intervention, and Referral to Treatment (SBIRT).**

SBIRT is a comprehensive, integrated, public health approach to the delivery of early intervention and treatment services for persons with substance use disorders. The utility of SBIRT for all forms of tobacco use, especially smoking, has been endorsed by the U.S. Preventive Services Taskforce. We will use a SBIRT approach to promote smoking cessation using the 5 “A”s (Ask, Advise, Assess, Assist and Arrange for Follow-up) that has been used in multiple settings and found to be particularly effective with tobacco and alcohol-use disorders.

**Screening and brief intervention:** Trained LHW case managers will oversee the screening and brief intervention procedures (i.e., the 5”A”s). The first “A” begins the intervention with the LHW “Asking” eligible clinic clients about smoking. When a participant reports being a daily smoker, the LHW will link the participant to a research assistant in the clinic who will obtain informed consent and enroll the smoker in the trial. The participant will return to the LHW case manager who will proceed to the next 3 “A”s (Advise, Assess, Assist). These 3”A”s will constitute the brief intervention. The LHW will utilize a motivational enhancing conversation focusing on increasing insight and awareness regarding smoking, offering information and Advice and Assessing motivation toward behavioral change. For those participants who are motivated for treatment, a referral (Assist) will be made to a clinic nurse prescriber (NPD) for evaluation for treatment with varenicline. For those not ready to make a quit attempt, the LHW will encourage consideration of quitting and Arrange for a follow-up conversation. A culturally acceptable standardized form will be integrated into intake procedures within the HIV clinic that will allow case managers to document implementation and outcomes of using the 5”A”s.

**Referral to treatment:** Treatment with varenicline will be offered and provided to those motivated to quit. Smokers will initiate medication treatment with varenicline with a quit date scheduled for day 8 following the first study dose of the medication. They will meet with the study clinician at baseline who will provide medical clearance and sign off on prescription orders. All medication will be provided to participants by the study team. Participants will receive a weekly supply of medication for the first four weeks to ensure proper dosing and monitoring for adverse events. For the subsequent 8 weeks, participants will return every 4 weeks to receive the next month’s supply of medication. Dosage adjustments will be permitted to control adverse effects throughout the trial. This will allow us to balance

internal validity with good clinical practice. The dosage of varenicline will be in accordance with package labeling.

Adverse events monitoring will be conducted by the study clinician each time a participant picks up their medication. The effectiveness of the referral process to specialized treatment is a strong measure of SBIRT success and involves a proactive and “warm handshake” between LHW case managers and clinicians to make sure the connection between PLWH and referrals are facilitated. LHW case managers will also provide cessation behavioral strategies, arrange follow-up check-ins to reinforce quitting for successful quitters, re-screen, and encourage cessation for those who do not succeed and return to earlier stages of change.

